#### Demographics and other potential confounders

Demographics and potential confounders will include age, parity, food insecurity, marital status, highest level of education attended, and language of survey administration. Age will be assessed as a continuous measure. Other measures will be categorical in nature. Parity will be classified as either having no live births, having one live birth, or having multiple live births. Past month food insecurity will be assessed as a binary (yes/no) item based on the question, “In the last 30 days, did you or any members of your household go without eating the whole day because there was not enough food?” Women both formally married and those cohabitating with a male partner will be considered married based on common practice. Highest level of schooling attended will be classified as primary or lower, secondary, or post-secondary.

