#### Recruitment and eligibility

Upon entering the clinic, female patients check-in for their appointment at the front-desk with the clinic receptionist who will offer the option to participate in a “women’s health study.” If interested in hearing more, the patient will be referred to a trained RA to complete recruitment. The RA will escorts the patient, alone without accompanying male partners or family members, to a location within the clinic that ensures visual and auditory privacy where they provide a brief description of the study and conduct eligibility screening. To be eligible for study enrollment, the patient must indicate that they are a) visiting the clinic “for family planning or are interested in receiving family planning” at their appointment that day, b) biologically female, c) age 15–49 years, d) not currently pregnant (self-report), e) not sterilized (self-report), f) have a male partner with whom they have had sex in the past 3 months, g) able to safely participate in a private interview without accompanying male partners or family members present, h) available for the 45 min necessary to conduct the interview, i) have no plans to move out of the area in the next 6 months, and j) have a mobile phone that can be safely used for re-contacting for follow-up surveys. As clients are recruited from general care, to be eligible for inclusion in follow-up surveys, participants must complete the immediate post-intervention (i.e. exit survey) and report having received contraceptive counseling on their exit survey.

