### Data analysis

We will adopt a difference-in-differences approach utilizing a multilevel, mixed-effects generalized linear regression, with logistic specifications for binary outcomes and linear specifications for continuous or scale outcomes, to evaluate associations between ARCHES intervention exposure and primary and secondary outcomes overtime. Longitudinal models will have fixed effects including time (baseline or follow-up), treatment arm, clinic, selected covariates, and a time and treatment interaction to indicate the treatment effect. These models will also take into account clusters (i.e. clinics) and clustering within clinics using nested random effects specifications to account for repeated measurements over time of individuals nested within clusters. The comparisons of outcomes at a single time point (e.g. immediately post-intervention) will use a similar multilevel mixed-effects regression approach, with single-level random effect specifications only for clinic, and only a fixed treatment effect (rather than time by treatment comparison). Final analyses will adjust for potentially relevant covariates (age, parity, food insecurity within the past 30 days, marital status, highest level of education attended, language of survey administration), in addition to time and treatment condition. Descriptive and bivariate analyses will be used to assess frequencies of and differences in demographics by treatment and loss to follow-up. Any characteristics identified as significantly associated with treatment or loss to follow-up at the *p* < 0.20 threshold will be considered as potential covariates (fixed effects) in adjusted models assessing effects of the intervention. Backwards selection at *p* < 0.20 will be used to finalize inclusion of potential covariates in regression models. Collinearity of covariates will be assessed, and highly collinear covariates may be removed from final models.

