The primary analyses will use an intent-to-treat approach and analyze all subjects according to treatment group. Exploratory analyses will also be run stratified by age group (adolescent girls and young women age 16 to 24; adult women age 25 to 49). Missing data on demographics and birth history may be computed where alternate data is available (e.g. calculating age from date of birth if age is not provided); however, no missing data will be imputed. All scales to be used as outcomes will be assessed for internal reliability at baseline using exploratory factor analysis and Cronbach’s alpha. If scales are identified as multifactorial or not internally reliable, they may be modified to more accurately reflect the intended construct and/or be presented as individual item outcomes. An α level of 0.05 (i.e. 95% confidence intervals exclusive of one) will be considered the threshold for statistical significance in all analyses. Analyses will be conducted using STATA version 14.2® (StataCorp LLC, 2015) [48] and SAS version 9.4® (SAS Institute Inc., 2018) [49].

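### The protocol does not say whether its six named confounders are exempt from p<0.20 covariate selection, in a non-randomized comparison; separately, the exploratory age strata leave out 15-year-olds

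*Protocol article*

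**What the plan says.** All of this is in the protocol article.

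- **Named list.** The section on demographics and other potential confounders gives it in one sentence: "Demographics and potential confounders will include age, parity, food insecurity, marital status, highest level of education attended, and language of survey administration".
- **Commitment to adjust.** Data analysis: "Final analyses will adjust for potentially relevant covariates (age, parity, food insecurity within the past 30 days, marital status, highest level of education attended", with language of survey administration as the sixth item.
- **Screen.** The same paragraph continues: "Any characteristics identified as significantly associated with treatment or loss to follow-up at the" p<0.20 level become candidates for the adjusted models.
- **Final selection.** Backwards selection, again at p<0.20, "will be used to finalize inclusion of potential covariates in regression models".
- **Further removal.** "Collinearity of covariates will be assessed, and highly collinear covariates may be removed from final models".
- **Allocation.** Assignment of clinics to treatment conditions reports that randomization within pairs was not acceptable to the implementers, that clinics nearer headquarters were more likely to get the intervention, and that women fall into an arm through the clinic they visit. Pairs were matched on patient volume, patient characteristics (wealth, age, services sought) and community type.
- **Age.** Recruitment and eligibility admits "c) age 15–49 years", and Informed consent describes a parental-consent waiver for ages 15 to 17. The exploratory strata in Data analysis are "adolescent girls and young women age 16 to 24; adult women age 25 to 49".

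**The concern.** A promise to adjust for six covariates and a rule that lets p-values settle which covariates stay in give the same model only if all six survive, or if the six are outside the rule. The text does not say that they are outside it. The adjusted model behind the primary results is therefore not fixed in advance.

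This matters more here than in a randomized trial. With three clinics per arm, non-random allocation and self-assignment by clinic, differences in patient mix between arms are to be expected. A p-value threshold asks whether a covariate's own association reaches significance. It does not ask whether leaving the covariate out biases the arm effect. A moderate confounder can fail the first test and still matter for the second.

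The exposure differs by outcome. RC and IPV have baseline values and a time-by-treatment contrast. Contraceptive uptake, a primary outcome, is measured once at the exit survey and modelled with a single treatment effect, a clinic random effect and covariates. Pregnancy, use of IPV services and leaving a relationship are also analysed on follow-up values only.

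The age strata are a separate, smaller matter: a participant aged 15 belongs to neither stratum.

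**Working it through.** **1. The two covariate rules side by side.** The adjustment sentence lists age, parity, food insecurity, marital status, education and survey language. These are the same six variables as in the confounder section. The screen follows directly on a sentence about differences in demographics, which is the confounder section's own heading for those six. The model description speaks of selected covariates. No sentence forces the six in.

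**2. How often would a real confounder be dropped?** The protocol gives no covariate effects, so these are assumptions: a binary covariate with 30% prevalence (variance 0.3 × 0.7 = 0.21), one observation per woman, no clustering.

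SE = 1/√[n·p(1−p)·0.21]; P(drop) = P(|Z| < 1.2816), where Z has mean ln(OR)/SE and unit variance.

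Example: n = 600 (target sample), p = 0.171 (the RC prevalence in the power section), OR 1.5. SE = 1/√(600 × 0.171 × 0.829 × 0.21) = 0.237; mean = 0.405/0.237 = 1.71; P(drop) = 0.33.

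| n | Outcome prevalence | OR 1.25 | OR 1.5 | OR 2.0 |
|---|---|---|---|---|
| 600 | 17.1% | 0.62 | 0.33 | 0.05 |
| 600 | 12.4% | 0.66 | 0.41 | 0.10 |
| 408 | 17.1% | 0.67 | 0.44 | 0.13 |
| 408 | 12.4% | 0.70 | 0.51 | 0.20 |
| 600 | 50% (assumed uptake) | 0.51 | 0.16 | 0.01 |
| 600 | 70% (assumed uptake) | 0.55 | 0.21 | 0.01 |
| 600 | 90% (assumed uptake) | 0.68 | 0.46 | 0.15 |

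The 12.4% is the mean of 17.1% and the 7.6% that OR 0.4 implies. The 408 is the protocol's required number retained. The RC rows overstate dropping to the extent that repeated measurements add information.

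**3. What does dropping do to the arm effect?** Null simulation, 2,000 runs per row: 600 women, six independent 30%-prevalence covariates, each more common in one arm by 10 or 15 points and all in the same direction, outcome prevalence about 70%, backwards selection at p<0.20. The preliminary screen and clustering were not simulated.

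| Covariate OR | Imbalance (points) | Runs dropping at least one | Mean dropped of 6 | Log-OR bias, selected (all six) | Type I error, selected (all six) |
|---|---|---|---|---|---|
| 1.25 | 10 | 99% | 3.28 | 0.030 (−0.001) | 0.058 (0.050) |
| 1.25 | 15 | 99% | 3.25 | 0.042 (−0.003) | 0.071 (0.045) |
| 1.5 | 10 | 78% | 1.36 | 0.019 (0.000) | 0.063 (0.052) |
| 1.5 | 15 | 78% | 1.35 | 0.030 (0.001) | 0.059 (0.047) |
| 2.0 | 10 | 12% | 0.13 | 0.007 (0.004) | 0.048 (0.045) |
| 2.0 | 15 | 12% | 0.12 | −0.004 (−0.008) | 0.060 (0.059) |

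Cross-check: 1.36/6 = 0.23 dropped per covariate, against 0.21 from the formula at 70% and OR 1.5. Monte Carlo error on a 5% rate is √(0.05 × 0.95/2000) = 0.5 points.

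A second null simulation ran the full two-step rule (800 runs per setting; 600 women; imbalances 0.10 to 0.15 SD; log-odds coefficients 0.10 to 0.20). It kept 1.4 to 2.9 of the six on average. Log-OR bias was 0.020 to 0.036, against −0.002 to 0.009 with all six, and rejection was 4.8 to 6.1% against 4.2 to 5.0%.

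**4. Scale.** The largest bias, 0.042, is an odds ratio of e^0.042 = 1.04. The unclustered standard error at 70% prevalence is √[2/(300 × 0.21)] = 0.18, so the bias is about 0.24 of a standard error.

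**5. Age coverage.** Ages 15 to 49 are 35 single years; 16 to 24 plus 25 to 49 are 9 + 25 = 34. Age 15 is missing.

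**6. Sample size.** The stated 408, 544 and 600 do not depend on any of this.

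**The case against.** **The six may be fixed already, or may be only a candidate pool.** On one reading the six are always in and selection covers extras; then none is lost, except perhaps for collinearity. On another, they are a named pool followed by a pre-stated algorithm, which is a choice of method and not a contradiction. Both readings are open. What stands is that the text does not choose between them, and that the second lets named confounders go.

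**Adjustment is not the only protection.** A reader might infer that covariates are the sole control of confounding. The protocol does not support that: clinics were matched, with age among the factors, and difference-in-differences with clinic effects removes much time-fixed confounding for RC and IPV. This stands, and narrows the point mainly to uptake.

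**Selection separately for each outcome is not stated.** A reader might infer a different model for every outcome. The text does not say whether selection runs once or repeatedly, and the screen uses treatment and loss to follow-up, not outcomes.

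**The numbers are small and rest on assumed inputs.** This stands. The simulations omit clinics, pairs and repeated measures. With 800 runs the Monte Carlo error is about 0.8 points, so part of that type I error gap may be noise.

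**Removing all data-driven selection has a price.** With 25% loss expected at six months and no imputation, predictors of loss may belong in the main models. This stands and shapes the fix.

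**Conclusion.** The concern holds in a limited form. The protocol names six covariates for adjustment and then lets a p<0.20 procedure settle inclusion without exempting them, so the adjusted model is open to the data and can lose a named confounder. The probable consequence is modest: a log odds ratio bias of up to about 0.04 and type I error up to about 0.07, under assumed covariate effects and imbalances that all run in one direction. For strong covariates (OR 2.0) the effect nearly vanishes. The weight falls on contraceptive uptake, and among secondary outcomes on those without a baseline value. The stronger reason to act is that the primary adjusted model should be known beforehand when allocation was not random.

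The age gap is a plain inconsistency of small consequence. A reader might infer that 15-year-olds are lost from the trial's results. They are not: the stratified analyses are labelled exploratory, and these girls remain in the primary analyses. Their expected number is not given.

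**What to change.** 1. State that age, parity, food insecurity, marital status, education and survey language are always included in the adjusted models and are not subject to the p<0.20 screen or to backwards selection.
2. Limit data-driven selection to additional characteristics, such as other predictors of loss to follow-up, or to sensitivity analyses.
3. Do not add the baseline outcome as a covariate in the longitudinal models. Baseline is already a response there, and the time-by-treatment term is the effect.
4. Change the younger exploratory stratum to 15 to 24.

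Cost: wording, with no change to the sample size. The six take about eight parameters: age 1, parity 2, food insecurity 1, marital status at least 1, education 2, language 1. Sparse subgroup outcomes, such as leaving a relationship, may not support that many. A reduced set for those outcomes should be named in advance.

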### Power calculations and sample size

Based on the pilot data from 143 female FHOK patients ages 15–49 years, prevalence of RC within the past 12 months was estimated at 17.1%. In a large U.S. cRCT, clients receiving the ARCHES intervention experienced a 0.4 reduction in odds (equivalent to an 8 percentage point reduction in intervention group reporting) of RC during the prior 3 months [23]. The present study is designed to achieve 80% power to detect a reduction of this magnitude (OR 0.4) related to past 3-month RC experience. Calculations assumed three control and three intervention clusters. Cluster size was assumed to differ in the range of 50–250 individuals per cluster, with a mean number per cluster of 100; the coefficient of variation for cluster sizes was thus set at 0.5. We anticipated low intra-class correlation (ICC) based on previous ARCHES trials (ICC < 0.01%) [23]. To be somewhat more conservative, we assumed an ICC of 0.1%. Under these parameters, the required average cluster size was 68, for a total of 204 control and 204 intervention participants (total required *N* = 408) retained at final follow-up. In previous ARCHES trials, retention was > 90% at 3-months follow-up; we assumed 85% retention at 3-months follow-up relative to baseline and 75% retention at 6-months follow-up relative to baseline, for an initial minimum N of 544. Our target final sample of 600 individuals exceeds the sample size required based on this conservative calculation.

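### The exploratory age analysis is set up as two separate significance results at 0.05, with no estimate of whether the effect differs by age

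*Protocol article*

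**What the plan says.** The protocol article deals with age subgroups in one sentence under Data analysis: "Exploratory analyses will also be run stratified by age group", with the groups given as "adolescent girls and young women age 16 to 24; adult women age 25 to 49". The same paragraph sets the threshold: "An α level of 0.05 (i.e. 95% confidence intervals exclusive of one) will be considered the threshold for statistical significance in all analyses". Exploratory analyses are not exempted from it.

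The preceding paragraph lists the model terms. For longitudinal outcomes the only interaction is "a time and treatment interaction to indicate the treatment effect". For outcomes measured once, such as contraceptive uptake at exit, there is a treatment effect and no interaction. No term involving treatment and age group is named; age appears only as a possible adjustment covariate.

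Under Power calculations and sample size, the trial is sized for 80% power to detect an odds ratio of 0.4 for past-3-month RC. The calculation starts from a pilot prevalence of 17.1% and three clinics per arm. The article does not say what share of participants is expected in each age group.

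**The concern.** The natural reason to split by age is to see whether ARCHES works differently in younger and older women. Two stratum-level significance results cannot answer that. One stratum crossing 0.05 while the other does not is weak evidence of a difference, because each stratum has far less power than the whole trial and either can miss by chance.

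At stake is how an exploratory table is read. Under Dissemination of results, findings go to the health ministry, regional stakeholders and federation members to inform scaling and replication. A table with one significant and one non-significant age group invites the reading that the programme works in only one of them, and the plan as stated supplies no number to set against that reading.

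**Working it through.** **1. Reproduce the design figure (Power calculations and sample size).**
Inputs: control prevalence 0.171, odds ratio 0.4, two-sided 0.05, 80% power, mean cluster size 68, ICC 0.001, coefficient of variation of cluster size 0.5.
- Control odds 0.171/0.829 = 0.2063; times 0.4 = 0.0825; intervention prevalence 0.0825/1.0825 = 0.0762.
- Two-proportion formula with pooled variance and no continuity correction: 189 per arm.
- Design effect 1 + ((1 + 0.5²) × 68 − 1) × 0.001 = 1.084.
- 189 × 1.084 = 204.9, against 204 stated. Power at 204/1.084 is 80.0%. 408/0.75 = 544, as stated.

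The 80% overall power is therefore taken as the article intends it.

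**2. Power within a stratum.**
At 80% power the expected z statistic is L = 1.96 + 0.84 = 2.80. A stratum holding a share f of participants has expected z of L√f and power Φ(L√f − 1.96). With f = 0.5: 2.80/√2 = 1.98, so power is Φ(0.02) = 50.8%.

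**3. Chance that the strata disagree when the true effect is the same in both.**
P(exactly one) = pₐ(1 − p_b) + p_b(1 − pₐ), treating the strata as independent. With equal strata:
- exactly one significant: 2 × 0.508 × 0.492 = 50.0%
- both: 0.508² = 25.8%
- neither: 0.492² = 24.2%

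Using the article's own proportions instead of the normal shortcut, 204 per arm gives 52.2% power per stratum and a 49.9% chance of exactly one. With 225 per arm (600 × 0.75 / 2) the chance is 49.3%.

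**4. Range over what the article does not give.** Chance of exactly one significant stratum:

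| Overall power | 50:50 | 40:60 | 30:70 | 20:80 |
|---|---|---|---|---|
| 50% | 40.6% | 41.0% | 42.2% | 44.1% |
| 80% | 50.0% | 51.2% | 54.9% | 60.8% |
| 90% | 46.6% | 48.5% | 54.0% | 62.7% |

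The power range matters because the planned analysis is a difference-in-differences, not a single follow-up comparison. A log-odds approximation at 204 per arm, with assumed within-person correlations of 0, 0.3 and 0.5, gives overall power of 56%, 71% and 84%. The chance of exactly one significant stratum (50:50) is then 44%, 49% and 50%.

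**5. If the common effect is zero.** Each stratum is significant with probability 0.05, so exactly one is significant with probability 2 × 0.05 × 0.95 = 9.5%.

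**6. What an interaction gives.** A valid interaction test at 0.05 wrongly indicates an age difference 5% of the time per outcome, whatever the common effect. It is imprecise. With equal strata each stratum's standard error is √2 times the overall one, so the difference has √(2 + 2) = 2 times the overall standard error. At the design effect the overall standard error on the log-odds scale is |ln 0.4|/2.80 = 0.916/2.80 = 0.327. The 95% interval for the difference therefore extends ±1.96 × 0.654 = ±1.28, a factor of about 3.6 either way on the odds-ratio scale.

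**The case against.** The strongest objection is that the article contains no such misreading. It labels the analysis exploratory, its hypotheses include no age contrast, and it nowhere says that the strata will be compared or that significance in one alone will be called an age difference. The subgroup expected to gain most is women reporting violence or coercion at baseline, not an age group. The article is condensed, and an interaction test may sit in a full protocol or SAP that is not shown. This largely stands: the risk is one of interpretation, and the absence of an interaction test alone would not be a point. What remains is that the published text chooses stratification as the method and applies 0.05 to it without exemption.

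A reader might go further and infer that a chance split would steer the programme towards or away from young women. The article does not support that. Under Control condition, scale-up follows if the intervention proves efficacious, and the intervention is described as delivered to all women and girls.

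A reader might also take 50% as the error rate whenever the effects are equal, or one-only as always the likeliest pattern. Neither is right. The figure is 9.5% under a common null. With equal strata, neither significant is likeliest at 50% overall power (51% against 41%), and both significant is likeliest at 95% power (0.722² = 52% against 40%).

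**Conclusion.** The point holds in a limited form. As stated, the age analysis produces two stratum-level significance results and no estimate of the difference between them. If a common effect of design size exists, exactly one stratum will be significant about half the time with equal strata, and about 41% to 63% of the time over the splits and powers tabulated.

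These figures rest on three assumptions: a real effect that is the same in both groups; power as calculated for RC only, from a 12-month prevalence applied to a 3-month outcome; and independence between strata, which is approximate because both age groups come from the same six clinics. With a real common effect, the significant stratum is a true positive. The error would lie only in concluding that the other group differs.

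Severity is minor: the analysis is exploratory and no decision is tied to it.

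**What to change.** For the exploratory age analysis, fit one model per outcome with an age-group interaction: treatment by time by age group for longitudinal outcomes, and treatment by age group for outcomes measured once, such as uptake at exit. Report each age group's estimate with its 95% interval, and the between-group difference with its own interval. State that stratum results are descriptive and that an age difference will be claimed only from the interaction.

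The same sentence needs one further repair: the age bands start at 16 while eligibility starts at 15, so the groups should be defined to include every participant.

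The cost is a sentence or two and no extra data. The trial gives up stratum-by-stratum significance statements and must accept a wide interval for the difference. That width shows how little a trial of this size can say about age differences.

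If the full protocol or SAP already specifies such an interaction, it is enough for the article's wording to be brought into line with it.
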